# Evaluating the myopia progression control efficacy of defocus incorporated multiple segments (DIMS) lenses and Apollo progressive addition spectacle lenses (PALs) in 6- to 12-year-old children: study protocol for a prospective, multicenter, randomized controlled trial

**DOI:** 10.1186/s13063-020-4095-8

**Published:** 2020-03-19

**Keywords:** Myopia, Progression, Prospective, Multicenter, Trial, Myopic defocus, Spectacle lens

## Abstract

**Background:**

Myopia is increasing in prevalence and is currently recognized as a significant public health issue worldwide, particularly in China. Once myopia develops, appropriate clinical interventions need to be prescribed to slow its progression. Currently, several publications indicate that myopic defocus (MD) retards eye growth and myopia progression. However, no clinical trials have compared the outcomes of different MD spectacle lenses in the same observational group, especially in mainland China. The aim of the present study is to compare the myopia control efficiency of two different MD spectacle lenses: defocus incorporated multiple segments (DIMS) lenses and Apollo progressive addition lenses (PALs).

**Methods:**

The trial is designed as a 3-year, prospective, randomized, multicenter clinical trial of schoolchildren treated with DIMS lenses and PALs. A total of 600 Chinese primary school children aged 6–12 years will be recruited, and each group is intended to include 300 subjects. The inclusion criteria are myopia between − 1.00 and − 5.00 diopters and astigmatism ≤ 1.50 diopters. The follow-up time points will be 1 month (m), 3 m, 6 m, 12 m, 18 m, 24 m, 30 m, and 36 m. The primary outcome will be determined by the difference between the two groups in cycloplegic spherical equivalent refraction between baseline and the last follow-up visit. The secondary outcome is the axial length, and the exploratory outcomes include ocular biometric measures, peripheral refraction, binocular vision, accommodation, compliance, and the results of questionnaires related to wearing experiences.

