### Eligibility criteria

The following eligibility criteria for this trial were modified from those provided by the International Myopia Institute (IMI) and related studies [6, 10, 15]:
Mainland Chinese, Han nationalityAge at enrollment: 6–12 years oldCycloplegic SER: − 1.00 to − 4.00 diopters, with SER calculated as the sphere plus 0.5 times the cylinder in diopters (Recommended dosage for cycloplegic refraction is two drops of 1% tropicamide given 5 min separately. Cycloplegic refraction outcomes should be measured 30–45 min after the first drop of tropicamide is instilled, which ensures the maximal cycloplegic effect.)Astigmatism: 1.50 diopters or lessAnisometropia: 1.50 diopters or lessDifference between the right and left pupil sizes: 2 mm or lessMonocular best-corrected visual acuity (BCVA): 20/20 (0.0 logMAR) or better (logMAR chart)Willingness to wear spectacle lenses regularlyAcceptance of random group allocation and the masked study design

The exclusion criteria are as follows:
Strabismus: checked by cover test at far and near distancesAny ocular and systemic diseases, including abnormalities, that might affect visual functions or refractive developmentPrevious experience with myopia control, including orthokeratology, progressive addition spectacle lenses, bifocal lenses, and pharmaceutical treatment (e.g., atropine)

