#### Primary outcome

The primary outcome is to determine whether DIMS lenses are noninferior to PALs for the prevention of myopia progression by evaluating the cycloplegic SER changes in two groups of subjects. For the primary outcome analyses, myopia progression over 3 years will be determined by the difference in the subjective SER between baseline and the last follow-up visit. Other measurements obtained at follow-up visits are considered secondary outcome measures.

Procedures for subjective refraction will be as follows [10]:
Starting with autorefraction and refine subjectivelyOcclude the left eyeDetermine best sphere firstDetermine cylindrical errorRefine sphere using + 1.00 diopter blur back test monocularly and finish by offering a binocular + 0.25 diopters additionalBinocular balance (prism dissociation); stop when no difference between the upper and lower line

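### The abstract and the eligibility list state different upper myopia limits for entry (−5.00 D and −4.00 D), so the target population is stated inconsistently

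*Protocol article*

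**What the plan says.** The Methods paragraph of the abstract states: "The inclusion criteria are myopia between − 1.00 and − 5.00 diopters", with astigmatism of at most 1.50 D. It does not say whether the figure is sphere, SER or another measure, or whether it is cycloplegic.

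The Eligibility criteria section is more specific. It names cycloplegic SER, starts the range at −1.00 D and ends it at minus "4.00 diopters, with SER calculated as the sphere plus 0.5 times the cylinder in diopters". It sets the same astigmatism limit as the abstract, 1.50 D.

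No other section gives an entry range, explains the difference or says which statement governs. The Trial status section names an ethics-approved protocol, version V1.0, which is not shown.

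The primary endpoint is on the same scale as the disputed limit: "myopia progression over 3 years will be determined by the difference in the subjective SER between baseline and the last follow-up visit".

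**The concern.** Both statements are current text, and both give a definite figure for a core entry criterion. They agree on the lower myopia limit and on astigmatism, so they appear to describe the same set of criteria. Only the upper myopia limit differs.

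Three things are at stake.

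- **Who the result applies to.** A reader of the abstract would take the trial to cover children up to −5.00 D. A reader of the eligibility list would stop at −4.00 D.
- **What counts as a deviation.** The Data management and data analyses section keeps every randomized participant in the analysis regardless of protocol adherence. A child enrolled between the two limits would stay in the analysis, and whether that child is recorded as an eligibility deviation depends on which statement is used.
- **Consistency of screening.** Five sites recruit through ophthalmologist and optometrist referral. Two published limits leave room for different referral and screening practice.

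**Working it through.** The plan has no derived figure to reproduce here. The check compares the two statements and tests whether a difference of measure could explain them.

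**Inputs**

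| Item | Abstract, Methods | Eligibility criteria |
|---|---|---|
| Measure | not named | cycloplegic SER |
| Lower myopia limit | −1.00 D | −1.00 D |
| Upper myopia limit | −5.00 D | −4.00 D |
| Astigmatism | at most 1.50 D | at most 1.50 D |

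The SER formula in the Eligibility criteria section is SER = sphere + 0.5 × cylinder. The section does not say whether cylinder is written in minus or plus form, so both are tested.

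**Step 1: size of the gap.** The upper limits differ by 5.00 − 4.00 = 1.00 D. The permitted range is 4.00 − 1.00 = 3.00 D wide in the eligibility list and 5.00 − 1.00 = 4.00 D wide in the abstract. The ratio is 4.00/3.00 = 1.33, so the abstract's range is one third wider.

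**Step 2: could the abstract mean sphere and the list SER?** Take a sphere of −5.00 D and the full permitted range of cylinder.

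- Minus-cylinder form, cylinder 0 to −1.50 D: SER runs from −5.00 D to −5.00 − 0.75 = −5.75 D.
- Plus-cylinder form, cylinder 0 to +1.50 D: SER runs from −5.00 D to −5.00 + 0.75 = −4.25 D.

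The least myopic SER that a −5.00 D sphere can give is therefore −4.25 D, which is still outside −4.00 D. Plus-cylinder sphere is the power of the more myopic meridian, so this case also covers reading the abstract's figure as the worst meridian.

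**Step 3: the same test in reverse.** Fix SER at −4.00 D. In plus-cylinder form with 1.50 D of cylinder, the sphere is −4.00 − 0.75 = −4.75 D. In minus-cylinder form, it is −4.00 + 0.75 = −3.25 D. No child within the list's limit reaches a sphere of −5.00 D in either notation.

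**Step 4: who is affected.** With the abstract's figure read as SER, children with SER beyond −4.00 D and up to −5.00 D are eligible under the abstract and ineligible under the list. The documents give no baseline distribution of SER, so the share of children in that band cannot be derived.

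**Step 5: timing.** Recruitment was scheduled from 30 October 2019, and the article is dated 19 March 2020, between four and five months later. At the planned average of ten children per month at each of five sites (50 per month), that is 4 × 50 = 200 to 5 × 50 = 250 of the 600 children. This is the planned rate, not a report of actual enrolment. On that schedule, settling the limit before the first enrolment was no longer possible at publication.

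**The case against.** The strongest reply is that the abstract is a one-line summary, while the Eligibility criteria section is the only detailed list. That section names the measure, the formula and the cycloplegia method. Nothing shows that sites work from a journal abstract. They would be expected to use the ethics-approved protocol, and the article describes central training, central form development and site-management staff from the lead hospital to keep conduct uniform. On this view there is a slip in one place and no practical consequence.

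Much of this stands. A reader might infer that sites are enrolling two different populations, or that the trial has no defined population at all. The documents support neither. Divergent enrolment is a possibility only, and the eligibility list is itself a full definition.

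A reader might also infer that the comparison between lenses is biased or the sample size wrong. That does not follow either. Children are allocated 1:1 from whichever population is enrolled, and the sample size inputs do not use the entry range.

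The reply does not remove the contradiction. It offers a reason to expect that the list governs, but the article does not say so, and V1.0 is not available to settle it. The one-third wider range compares interval widths only and says nothing about how many children are involved.

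**Conclusion.** The inconsistency is real and should be corrected. The upper entry limit is −5.00 D in the abstract and −4.00 D in the eligibility list, and no reading as sphere, worst meridian or SER brings the two together. The size is a 1.00 D band of SER in which eligibility depends on the section read. The number of children in it is unknown.

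The consequence is limited to how the target population is described, how far the result can be generalized and how eligibility deviations are recorded. The planned number of participants and the randomized comparison are not directly affected.

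The conclusion rests on the article's own SER formula and its 1.50 D astigmatism limit. It does not depend on which of the two limits was intended, and the documents do not show that.

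**What to change.** 1. Compare both places with ethics-approved version V1.0 and correct whichever departs from it. State one limit in the abstract and in the eligibility list, and name the measure (cycloplegic SER) in both.
2. Because recruitment was scheduled to be under way by publication, ask each site which limit it has applied. Report the number of children enrolled with SER beyond −4.00 D and up to −5.00 D, by arm and site, and say how they are classified.
3. As a separate improvement, adjust the primary analysis of SER change for baseline SER. The Data management and data analyses section names a repeated measures analysis of variance and mentions no baseline covariate. This does not resolve the eligibility conflict. It accounts for differences in starting refraction and can gain precision, but the documents do not give the correlation needed to say how much.

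The cost is a wording correction, one query to five sites and one extra model term. Baseline cycloplegic refraction is already in the schedule of assessments (Table 1), so no new data are needed.

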**Discussion:**

The present study will be the first randomized controlled trial in myopic primary school children treated with DIMS lenses and PALs in China. The results will indicate whether and how much different MD mechanisms retard myopia progression and axial elongation. In addition, the comparison will provide information on the clinical efficacy and safety of DIMS lenses and PALs, including information related to wearing experiences and visual function.

**Trial registration:**

Chinese Clinical Trial Registry (ChiCTR), ChiCTR1900025645. Registered on 3 September 2019. http://www.chictr.org.cn/showproj.aspx?proj=42927.

## Background

It is estimated that myopia (also called “nearsightedness”) will affect 50% of the world population by 2050 [1–3]. With the growing prevalence of myopia in young generations, this “epidemic” disease is currently recognized as a public health issue, particularly in China [4]. The annual incidence of myopia onset between the ages of 7 and 15 years is constantly growing, and by the age of 18 years, ~ 80% of the urban-based Han population in mainland China is myopic, regardless of geographic locality. Controlling the progression of myopia and preventing complications of myopia that result in irreversible visual loss, such as myopia maculopathy, retinal detachment, glaucoma, and cataracts [5], will require collaborative efforts worldwide.

Several clinical interventions are currently used for myopia control, including spectacle lenses, contact lenses, and pharmacological treatments [6]. Regardless of the treatment strategy, slowing the progression of myopia after onset is the most important therapeutic goal [1, 4]. It has been reported that single-vision (SV) spectacle lenses designed to alter peripheral defocus achieve less than a 14% reduction in myopia progression. Bifocal vision and progressive addition spectacle lenses have shown variable clinically significant therapeutic effects between 6% and 50% compared with SV spectacles in different studies [7, 8]. Orthokeratology has proven to be effective in slowing myopia progression and axial elongation by between 30% and 55% [7]. Additionally, 0.01% atropine has shown an effect on refractive error retardation (~ 45%) and no apparent effect on axial length compared with historical control groups [7, 8].

Once a child has been diagnosed with myopia, an appropriate management strategy should be applied. In addition, several other aspects should be taken into account, such as age of onset, baseline refractive status, visual environment, compliance, risks and benefits of the treatment strategy, parental myopic status, and annual cost [7, 8]. Among all the treatment options, intervention with spectacle lenses is a simple as well as the least invasive method, in contrast to contact lenses and pharmacological treatments, for children and their parents, especially for children under 8 years old [7]. Considering numerous patient-specific factors related to myopia development and progression, the optimum prescription needs to be verified according to associated risk factors [4, 7].

Currently, there are several publications from animal and human studies showing that myopic defocus (MD) retards eye growth and myopia progression, while hyperopic defocus promotes eye growth compared with SV spectacle lenses [9–12]. In clinical, there are two major spectacle lenses designs based on the idea of MD: defocus incorporated multiple segments (DIMS) lenses and Apollo progressive addition lenses (PALs) (Apollo Eyewear, River Grove, IL, USA) [10, 13, 14]. Both are recommended to manipulate optical defocus across the visual field, which has been suggested to result in greater myopia control. However, to date, several issues remain under exploration, including (1) the efficacy of myopia control associated with added powers investigated systematically in the same observational, multicenter clinical trial; (2) the efficacy in 6- to 12-year-old primary school students in mainland China, who are especially prone to myopia progression; and (3) the quality of vision, which refers to the comfort and frequency of visual symptoms after wearing added-power spectacle lenses and is evaluated through questionnaires.

## Methods/design

### Aim of the study

The current prospective, multicenter randomized controlled trial will evaluate the myopia progression control efficacy of two broadly used clinical MD spectacle lenses (DIMS lenses and PALs) in 6- to 12-year-old myopic children in primary school. The primary aim is to determine whether DIMS lenses are noninferior to PALs in the combined endpoint of spherical equivalent refraction (SER) and axial length (AL) progression in myopic subjects over 3 years. Other changes will also be compared over the study period, including risk factors, ocular health, uncorrected relative peripheral refraction, binocular vision function (principally vergence), accommodation (particularly lag and amplitude), subfoveal choroidal thickness, visual environment, and wearing experiences [15].

### Study settings and responsibilities

Five trial sites will be involved, including Peking University People’s Hospital (PKUPH; [name], principal investigator [PI]; [name], co-PI), Peking University International Hospital ([name], sub-PI), Kunming City Maternal and Child Health Hospital ([name], sub-PI), Beijing Haidian Maternal and Child Health Hospital ([name], sub-PI), and ChuiYang Liu Hospital affiliated with Tsinghua University ([name], sub-PI). Each of the hospitals is a large center with ophthalmology clinics and optometrists, and data will be collected at each site. The primary investigators at each site compose the steering committee, which is under the leadership of PKUPH ([name], PKUPH, lead PI and chair). The steering committee will provide final approval of the protocol and any changes to the procedure during the clinical trial.

Among these sites, PKUPH will be in charge of supervising the conduct of the study, including staff training and assessment, protocol decisions and amendments, form development, data management, data analyses, and quality control. The reason for endowing PKUPH with this governance authority is that PKUPH has undertaken dozens of domestic and foreign multicenter clinical trials and thus has abundant clinical trial experience. In addition, PKUPH has a group of staff members who undertake site management organization (SMO) work, which will ensure that the clinical trial protocol will be strictly implemented at different study sites.

Coordinating responsibilities, such as data collection and recording, will be performed at all of the study sites. Subjects will be screened at each site to achieve a minimum screening percentage of 10% and a maximum percentage not exceeding 30%. All of the centers will continue to screen subjects until the target population is achieved.

### Study design and recruitment

This is designed as a 3-year, prospective, randomized, multicenter clinical trial. Recruitment is intended to begin on 30 October 2019 and is scheduled to end on 30 October 2020. A total of 600 primary school children (aged 6–12 years) will be recruited, and each of the participants will be followed for 3 years. Randomization will be performed with a random number table, and each group (DIMS or PALs) will contain 300 subjects. The final distance prescription will be determined by a masked investigator (MI) using the cycloplegic subjective refraction measured by phoropter after the objective refraction is measured by autorefraction. The lenses will be replaced with an updated prescription when the change in SER is greater than 0.50 diopters.

Potential participants will be recruited for the clinical trials at each center through two primary processes: (1) ophthalmologist referral during daily eye disorder treatment in outpatient clinics and (2) optometrist referral from optometry clinics during myopia treatment.

All of the potentially eligible participants and their parents/guardians will be contacted by a research coordinator who will explain the study in detail to ensure that the children and their parents/guardians understand the entire clinical trial. Once they are interested, both the patients and their parents/guardians will be seen in the clinical research laboratories to sign an informed consent form. Interested participants will be invited for the eligibility and baseline assessments by the study staff. All the identifying information will be confidential. It is estimated that ten new subjects will be recruited each month, on average, at each site.

### Myopia defocus spectacle lens systems and spectacle prescriptions

#### DIMS lenses

The DIMS lenses are custom-made plastic spectacle lenses. Each lens comprises a central optical zone (9 mm in diameter) for correcting distance refractive errors and an annular multiple focal zone with multiple segments (33 mm in diameter) having a relative positive power (+ 3.50 diopters). The diameter of each segment is 1.03 mm [10].

#### Apollo PALs

The Apollo PALs comprise an asymmetrical MD design with a 3 MD zone, including a + 2.50 diopters full positive power superior zone, an 80% full MD power nasal zone, and a 60% full MD power temporal zone.

Both of the spectacle lenses are designed to simultaneously provide clear distance vision for the wearer and introduce MD for the peripheral retina by providing a plane in front of the retina, resulting in signals being received as blurred images on the retina [5]. All of the children will be instructed to wear lenses all the time throughout the whole study. The use of atropine eye drops of any concentration will not be permitted for any participant during the study.

The final distance prescription of the spectacles will be determined on the basis of cycloplegic subjective refraction by the masked optometrist. The spectacle lenses will be replaced and upgraded when the change in SER is 0.5 diopters or more in either eye compared with refraction while wearing spectacles.

At the initial spectacle dispensing and at each follow-up visit, subjects and their guardians will receive face-to-face instruction about the purpose, use, and care of the lenses. In addition, investigators will explain the etiology and pathology of myopia, emphasize the importance of adherence to the follow-up protocol for evaluating myopia progression, and provide notifications regarding the follow-up ophthalmic examinations. In addition, the SMO from PKUPH will provide phone call reminders before each visit to enhance compliance with the present clinical trial.

### Eligibility criteria

The following eligibility criteria for this trial were modified from those provided by the International Myopia Institute (IMI) and related studies [6, 10, 15]:
Mainland Chinese, Han nationalityAge at enrollment: 6–12 years oldCycloplegic SER: − 1.00 to − 4.00 diopters, with SER calculated as the sphere plus 0.5 times the cylinder in diopters (Recommended dosage for cycloplegic refraction is two drops of 1% tropicamide given 5 min separately. Cycloplegic refraction outcomes should be measured 30–45 min after the first drop of tropicamide is instilled, which ensures the maximal cycloplegic effect.)Astigmatism: 1.50 diopters or lessAnisometropia: 1.50 diopters or lessDifference between the right and left pupil sizes: 2 mm or lessMonocular best-corrected visual acuity (BCVA): 20/20 (0.0 logMAR) or better (logMAR chart)Willingness to wear spectacle lenses regularlyAcceptance of random group allocation and the masked study design

The exclusion criteria are as follows:
Strabismus: checked by cover test at far and near distancesAny ocular and systemic diseases, including abnormalities, that might affect visual functions or refractive developmentPrevious experience with myopia control, including orthokeratology, progressive addition spectacle lenses, bifocal lenses, and pharmaceutical treatment (e.g., atropine)

